45 paralysis, fatigue and interpersonal sensitivity [15, 16]. Hence lipid-lowering effects of statins  
46 may also play a role in putative antidepressant effects of this class of drugs. Data from the  
47 STAR\*D trial indicate poorer treatment response to SSRIs in those with atypical depression  
48 and therefore, statins could provide genuinely novel therapeutic targets for this group of  
49 people with TRD [17].

50

51 We plan to carry out an RCT involving 150 participants with treatment-resistant depression,  
52 with the aim of determining whether the addition of simvastatin (20mg daily), a lipophilic  
53 statin that readily crosses the blood-brain barrier [18, 19], to treatment as usual (TAU) for 12  
54 weeks leads to a reduction in depressive symptoms compared with placebo added to TAU.  
55 We predict that treatment-resistant depression patients will show improvement in mood with  
56 simvastatin treatment and that the response will be associated with reduction in lipid  
57 biomarkers (i.e. plasma LDL and LDL/HDL ratio). A secondary hypothesis relates to  
58 simvastatin's effects on putative inflammatory biomarkers. High LDL and low HDL  
59 contribute substantially to immunological up-regulation in the development of  
60 atherosclerosis. Pro-inflammatory cytokine (Interleukin-6 and Tumour Necrosis Factor)  
61 levels are often altered in depressed patients and decreased by successful antidepressant  
62 therapy [20, 21]. We therefore predict that in those treatment-resistant depression patients  
63 who show improvement in mood with simvastatin treatment, that response will be associated  
64 with reduction in inflammatory biomarkers. Our mechanistic hypothesis is that the anti-  
65 inflammatory and lipid-reducing effects of simvastatin will improve neuroinflammation and  
66 thus mediate a response to simvastatin.

67   **Methods**

68   A pragmatic multi-centre, 12-week, double blind, placebo controlled randomised trial of  
69   simvastatin added to treatment as usual (TAU) for patients suffering from a DSM-5 major  
70   depressive episode that has failed to respond to at least two trials of antidepressants. This will  
71   be a parallel group study with 75 participants in each arm. Recruitment will occur at  
72   outpatient psychiatric clinics in Karachi, Lahore, Hyderabad, Rawalpindi and Quetta  
73   Pakistan. Consistency of procedures across sites will be ensured through vigorous training  

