#### 95 *Sample Size*

96 We estimate a moderate effect size of 0.60 will be reported at week 12. Assuming a type-1  
97 error of 5%, we will need to follow up 120 patients across the two groups to achieve 90%  
98 power at Week 12. With an anticipated dropout rate of 20% by Week 12, we will randomise  
99 150 participants. An effect size of 0.4 or greater for difference in MADRS scores in  
100 randomised controlled trials of antidepressants versus placebo has been suggested as  
101 necessary to suggest clinical utility for an antidepressant used as monotherapy. A sample of  
102 120 participants is therefore powered to detect moderate to large effect sizes and trends  
103 towards significance in areas of smaller effect.

104

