#### *Statistical Analysis*

Initial descriptive analysis will be conducted to study the profile of the subjects and investigate group differences at baseline on main demographics and clinical measures. Frequencies and proportions will be used for categorical variables and mean and standard deviations, median and inter-quartile range, minimum and maximum for continuous variables. No statistical significance tests will be used to compare groups. Drop out, visit frequency and adherence to treatment will be summarized by group with the appropriate descriptive statistics.

The main analysis will follow the Intention-to-treat (ITT) principle in which subjects are assigned to treatment groups as randomized. Subjects that drop out of the study will be included in the analysis provided that they have a baseline score for the outcome. For the primary hypothesis, the MADRS scores at week 12 will be compared between groups using a mixed effect model. The outcome for the model will be all post-baseline MADRS scores and the fixed effects will include baseline MADRS scores, treatment group, time (post-baseline timepoints) and a treatment group by timepoint interaction. To account for the dependencies between repeated measures on the same patients, an intercept for each individual will be included as a random effect. A linear contrast will be used to test the primary hypothesis, the difference between groups in at week 12 in MADRS scores. Given the modest sample size it will likely not be possible to use as random slope for each subject, however the covariance matrix of the residuals of the model can be allowed to correlate to account for dependencies across time. Two tailed tests and an alpha level of 0.05 will be used for significance. All estimates will be presented with the 95% confidence interval. To give an estimate of effect size, standardized regression coefficients will be calculated using the overall SD of the baseline outcome scores as the metric. One advantage of this approach is it gives the magnitude and direction of effect in units of patient population of interest.

275

276 Secondary analyses will use similar mixed models to that of the primary outcome, baseline  
277 adjusted with time, treatment group and the interaction between treatment group and time as  
278 independent variables. As for the primary outcome, the main timepoint of interest is 12 week  
279 follow up and treatment effects will be determined by contrasts at the measured timepoint.  

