The exploratory hypothesis that baseline lipid/CRP levels will affect response to simvastatin will be tested by adding the baseline lipid/CRP to a model for the primary outcome at 12 weeks, adjusted for baseline and including a treatment group by baseline lipid/CRP. The lipid/CRP level will be considered moderators if interaction with treatment group is significant (at significance level of 0.05, using bootstrapping for inference and construction of confidence intervals). If this is the case, exploratory plots that look at the group effect at different levels of the moderators will be used to study the nature of the moderation.

In order to test the hypothesis that changes in peripheral levels of lipids/CRP will be a mediator in the path between treatment and change in MADRS scores, an initial descriptive analysis will be conducted to look at the bivariate association between treatment group and change in lipid/CRP levels, and between change in lipid/CRP (at 4 and 12 weeks) and change in MADRS scores. A mediation model will then be fitted to the data that joint models the effects of treatment on the change in lipid/CRP at 4 weeks and MADRS at 12 weeks. The mediation effect is tested by the proportion of the total effect from treatment group to change in MADRS that goes through change in lipid/CRP. This model will be fitted in Lavaan in R or Mplus 7.11[35] and the indirect effect estimated through bootstrap resampling. Given the sample size, note the effect sizes for the indirect mediation pathway would need to be relatively large [36].

323

324 *Safety Monitoring*

325 Adverse events monitoring from the time informed consent is obtained until follow-up at 12  
326 weeks (using the side effect assessment scale). Laboratory parameters including total serum  
327 cholesterol, LDL, HDL, triglyceride, AST, ALT, LDH and CPK will be checked by the study  
328 physician before patient entry into the trial, and if there are any safety issues for which the  
329 patient should not be started on study medication, he/she will not be included to the study.

330

331 *Study coordination*

332 Local investigators will chair a weekly meeting with research assistants to help coordinate the  
333 study. The chief investigator will hold meetings with the research team every two weeks via  
334 Skype.

335

336 *Data protection and confidentiality*

337 For data security, consent forms and paper copies of assessment tools having any identifying  

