**Discussion**

At least a third of patients with MDD are treatment-resistant [2] and up to a third of patients also show evidence of an activated inflammatory response [37]. There is increasing evidence linking immune-metabolic disturbances to MDD. Numerous studies have demonstrated the anti-inflammatory effects of statins in altering cytokine release and phagocytic activity [38-43]. Simvastatin has been shown to be superior to alternative statins in preventing neurodegenerative conditions, due to its permeability across the blood brain barrier and ability to prevent against cell death [44]. Moreover, treatment-resistant depression (TRD) has been shown to be a neuroprogressive condition [45] yet despite clinical trials demonstrating simvastatin's potential efficacy as an adjuvant treatment for MDD [22], we are unaware of any clinical trials in TRD.

To our knowledge, the current trial will be the first trial investigating the use of simvastatin as augmentation strategy in patients with TRD. If this study indicates that adjuvant simvastatin is efficacious in reducing depressive symptoms, it will deliver immediate clinical benefit. It is an inexpensive, off-patent drug that is readily available worldwide. It could potentially be a cost-effective treatment option in settings with diminishing resources such as low- and middle-income countries as well as other publicly funded health care services. The results of the biomarker analysis may provide insights in to the mechanism of action of simvastatin and if reductions in plasma lipids and/or inflammatory biomarkers are associated with an individual response to adjuvant simvastatin, it could inform the development of a "precision medicine" approach to the treatment of TRD. Furthermore, the results of this study will inform the current evidence base of treatment options for patients with treatment-resistant depressive symptoms, a condition that causes significant disability and functional

impairment yet for which there is a clear paucity of controlled clinical trials of novel treatments.

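### The planned association between lipid/CRP change and MADRS change does not hold treatment arm fixed, so it cannot carry the patient-level biomarker predictions

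*Protocol*

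**What the plan says.** The mediation paragraph of the Statistical Analysis section opens with an initial step, labelled descriptive, that looks at two bivariate associations: treatment group with change in lipids/CRP, "and between change in lipid/CRP (at 4 and 12 weeks) and change" in MADRS scores. Neither adjustment for arm nor a split by arm is mentioned. A mediation model follows, with treatment acting on biomarker change at week 4 and on MADRS at week 12. Mediation is tested there through the proportion of the total effect, with a bootstrapped indirect effect. The section does not say whether the path from biomarker change to MADRS is conditional on treatment.

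The claims these analyses serve are about patients. The Background predicts improvement in mood with "simvastatin treatment and that the response will be associated with reduction in lipid" biomarkers, and makes a parallel prediction for inflammatory markers among those who improve on simvastatin. The Discussion adds that "if reductions in plasma lipids and/or inflammatory biomarkers are associated with an" individual response, this could inform a precision-medicine approach.

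**The concern.** Whether the patients whose markers fall are the patients whose mood improves is a question within arms. A correlation taken over both arms together mixes that link with the difference between the arm means. The trial tests a lipid-lowering drug and hopes that it also lowers MADRS. If it does both, marker change and MADRS change will be correlated over the whole sample even if they are unrelated among patients given the same treatment.

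At stake is the reading of the mechanistic results in a positive trial. The unadjusted association could be cited for individual, biomarker-linked response when it reflects only that the drug moved two things.

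**Working it through.** **The plan's own figure.** The Sample Size section states: "We estimate a moderate effect size of 0.60 will be reported at week 12". With two-sided 5% and 90% power, the normal approximation gives 2 × (1.960 + 1.282)² / 0.60² = 58.4, so 59 per arm. The t-based calculation gives 59.4, so 60 per arm and 120 in total. Power with 60 per arm is 0.903 (t-based). For dropout, 120 / 0.80 = 150. The plan's figures reproduce, and 60 per arm is used below.

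**Inputs.** The MADRS effect dY is 0.60 SD (planned), or 0.40 SD (the clinical-utility benchmark in the same section). Allocation is 1:1. The protocol gives no standardised effect dM on marker change, so a range of 0.2 to 2.0 SD is assumed. The within-arm correlation is set to zero.

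**Formula.** With half the patients in each arm, the covariance over the whole sample is the within-arm covariance (here 0) plus dM × dY / 4. The variances are 1 + dM²/4 and 1 + dY²/4. Hence

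r = (dM × dY / 4) / √[(1 + dM²/4)(1 + dY²/4)].

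At dM = 1.5 and dY = 0.60: 0.225 / √(1.5625 × 1.09) = 0.225 / 1.305 = 0.17.

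**Results.** Rejection rates come from 20,000 simulated trials per scenario, using a two-sided 5% test of the correlation as a yardstick.

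| dM (SD) | r, dY = 0.60 | p<0.05, dY = 0.60 | r, dY = 0.40 | p<0.05, dY = 0.40 |
|---|---|---|---|---|
| 0.2 | 0.03 | 6.1% | 0.02 | 5.5% |
| 0.5 | 0.07 | 11.8% | 0.05 | 8.2% |
| 1.0 | 0.13 | 28.7% | 0.09 | 15.7% |
| 1.5 | 0.17 | 47.5% | 0.12 | 25.3% |
| 2.0 | 0.20 | 62.0% | 0.14 | 33.4% |

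When the drug moves only one of the two measures, the pooled rate stays at about 5%. With the association taken within arm, the rate is 4.8% to 5.3% in every scenario.

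**The mediation model.** In the same no-link setting at dY = 0.60, a model whose marker-to-MADRS path is adjusted for treatment gives a mean indirect effect of about zero (4,000 simulated trials for each dM of 1.0, 1.5 and 2.0). If that path were left unadjusted, the apparent mediated share would be (dM²/4) / (1 + dM²/4). That is 0.25/1.25 = 20%, 0.5625/1.5625 = 36% and 1/2 = 50% at those three values; simulation gave 21%, 36% and 50%.

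**Which analyses adjust for arm.** The mediation model uses week-4 marker change only. The moderator analysis uses baseline marker level, not change. Week-12 marker change against MADRS change therefore appears only in the bivariate step. In addition, the Measurement of biomarkers section lists two blood samples, at baseline and week 12, while Table 1 also marks biomarkers at week 4. These must be reconciled. If no week-4 sample is taken, the mediation model as written has no mediator.

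**The case against.** The best defence is that the step is only descriptive. The sentence "Two tailed tests and an alpha level of 0.05 will be used for significance" stands in the account of the primary model, and nothing ties it to this step. The moderator analysis in the same section states its own 0.05 level and the mediation analysis names its own test; this step has neither. A reader might infer that the trial will report a falsely significant association, almost by construction. The document does not support that. No test is specified, and even if one were run, the rate at the planned effect is 6% to 62% over an assumed range, lowest for a marker the drug barely moves.

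It can also be said that the formal inference is the mediation model, which includes treatment, and that splitting a total effect normally conditions the mediator path on treatment. That stands: the unadjusted shares above show what would happen if the path were misspecified, not what the protocol plans. Nor is it a fault that a descriptive figure may differ from the model that follows it.

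Finally, bivariate does not strictly mean pooled, and the Background and Discussion statements name no analysis. Both are fair. Still, the stated form involves two variables with arm not among them, no split is mentioned, and no other planned analysis relates week-12 marker change to mood. Labelling the estimate descriptive does not make it the right quantity for a statement about individual response.

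**Conclusion.** The point holds in a limited form. As written, the association does not hold arm fixed, and if simvastatin lowers both measures it is partly a product of arm. At the planned 0.60 SD MADRS effect, and with assumed marker effects of 0.5 to 2.0 SD, the induced correlation is about 0.07 to 0.20; it would look nominally significant in about 12% to 62% of trials if tested. These figures assume no within-arm link, normal data, complete pairs for 60 per arm, and marker effects that the protocol does not give. One range has been applied to lipids and CRP alike.

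It does not follow that the mediation analysis is biased: the text leaves the conditioning of one path unstated but does not rule it out. The primary analysis and the sample size are untouched. What is affected is the week-12 association and any claim about individual, biomarker-linked response that leans on it.

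**What to change.** In the mediation paragraph of the Statistical Analysis section:

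1. Replace the bivariate marker–MADRS association with one from a model that includes treatment arm, at each planned marker time point, and show it separately by arm, all with 95% confidence intervals.
2. State that the marker-to-MADRS path in the mediation model is conditional on treatment.
3. State that no patient-level or mechanistic conclusion, including those foreshadowed in the Background and Discussion, will rest on the pooled association.
4. Reconcile the Measurement of biomarkers section with Table 1 on the week-4 sample.

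Items 1 to 3 cost one degree of freedom and a little extra analysis, with no new data. By-arm estimates will be imprecise: on Fisher's z scale the 95% half-width is 1.96/√57 = 0.26 with 60 patients, against 1.96/√116 = 0.18 for the arm-adjusted estimate with 120. Adjustment removes confounding by arm, not by other patient characteristics, so the result remains an association. The change is best made before unblinding.

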#### *Measurement of biomarkers*

Participants will be asked to provide two blood samples: at baseline and week 12. We aim to analyse the relationship of simvastatin to lipid and inflammatory markers and determine if this is associated with symptom change prior to a clinical effect (if detected). The biomarkers analysed will include lipid biomarkers HDL, LDL and C-Reactive Protein (CRP), a peripheral marker of inflammation.

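### The mediation model omits the early MADRS ratings, so it can overstate mediation and cannot show that biomarker change came before clinical effect

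*Protocol*

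**What the plan says.** The Statistical Analysis section of the Protocol fixes the mediator (lipid/CRP change at week 4) and the outcome (MADRS at week 12). Mediation is judged by the share of the total treatment effect on MADRS change that passes through the marker, with a bootstrapped indirect effect: "A mediation model will then be fitted to the data that joint models the" two treatment effects together. No interim MADRS rating, no other confounder of the marker-to-mood path and no sensitivity analysis is named.

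The aim, under Measurement of biomarkers, is to "analyse the relationship of simvastatin to lipid and inflammatory markers and determine if this is associated with symptom change prior to a clinical effect". Follow-up, Outcome measures and Table 1 place MADRS ratings at baseline and weeks 2, 4, 8 and 12. Writing of IL-6 and TNF, the Background says that their "levels are often altered in depressed patients and decreased by successful antidepressant" treatment.

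Measurement of biomarkers lists blood samples at baseline and week 12 only. Table 1 also ticks biomarkers at week 4.

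**The concern.** Randomisation protects the treatment-to-marker path. It does not protect the marker-to-MADRS path. A patient whose mood has already improved by week 2 or 4 will tend to score lower at week 12. If that improvement, or something behind it, also goes with a lower marker at week 4, then marker change and week-12 MADRS are correlated with no causal effect of the marker. Measuring the marker at week 4 and the outcome at week 12 does not remove this, because early mood can relate to both.

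For LDL, a statin should move the marker whatever its effect on mood, so the mediation result rests largely on the unprotected path. A model with no early measure of mood also cannot say whether the marker moved before mood did, which is the stated aim. The Discussion looks to the biomarker results for insight into mechanism and for a possible precision-medicine approach.

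**Working it through.** **1. The plan's own figure.** The Protocol gives no figure for the mediation analysis. Its sample size sets the number analysed: "We estimate a moderate effect size of 0.60 will be reported at week 12", two-sided 5%, 90% power, 20% dropout. Per arm, n = 2 × (1.96 + 1.2816)² / 0.60² = 58.4, so 59 per arm or 118 in total, against 120 stated. Power at 60 per arm is 0.90-0.91, and 120 / 0.8 = 150. The figures reproduce, and N = 120 is used below.

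**2. Assumptions, none of them in the Protocol.** The marker has no effect on mood. Baseline-adjusted MADRS correlations are 0.7 (weeks 2-4), 0.5 (2-12) and 0.6 (4-12). Within arm, the week-4 marker correlates r with mood at week 2 or at week 4. Treatment shifts the marker by d = 1 SD (LDL-like) or 0.3 SD (CRP-like). Mediation is claimed when both paths reach p < 0.05.

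**3. Model without early MADRS.**
- Treatment-to-marker path: z = d × √30. This is 5.48 for d = 1 (power about 1) and 1.64 for d = 0.3 (power about 0.38).
- Marker-to-MADRS path: the induced correlation is ρ = 0.5r if the marker tracks week-2 mood and 0.6r if it tracks week-4 mood, with z ≈ ρ√117 / √(1 − ρ²).
- False-mediation rate ≈ the product of the two rejection probabilities.

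| r | ρ (week 2 / week 4) | z | rate, d = 1 | rate, d = 0.3 |
|---|---|---|---|---|
| 0 | 0 | 0 | 5% | 2% |
| 0.1 | 0.05 / 0.06 | 0.54 / 0.65 | 8% / 10% | 3% / 4% |
| 0.2 | 0.10 / 0.12 | 1.09 / 1.31 | 19% / 26% | 7% / 10% |
| 0.4 | 0.20 / 0.24 | 2.21 / 2.67 | 60% / 76% | 22% / 29% |

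Simulation of the same setting agrees. For d = 1 it gives about 5%, 9%, 20-26% and 57-77%. For d = 0.3 it gives about 2% to 29%.

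**4. Week-2 MADRS added to the outcome equation.** The partial correlation is (ρ_MY − 0.5 ρ_M2) / √((1 − ρ_M2²) × 0.75), where ρ_MY is the marker's correlation with week-12 MADRS and ρ_M2 its correlation with week-2 MADRS.
- Marker tracks week-2 mood: the numerator is 0.5r − 0.5r = 0, so the rate returns to about 5% (d = 1).
- Marker tracks week-4 mood: the numerator is 0.6r − 0.35r = 0.25r. At r = 0.2 this gives 0.05 / 0.857 = 0.058, z = 0.63, rate 10%. At r = 0.4 it gives 0.10 / 0.831 = 0.120, z = 1.30, rate 26%. Simulation gives 9-26%.
- With weeks 2 and 4 both added, simulation gives about 5%.

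**5. A second design, closer to the planned test.** This used an interval for the indirect effect, a total effect of −0.6 SD, MADRS reliability of about 0.8 and a 1 SD treatment effect on the marker. Week-2 mood moved the week-4 marker by 0 to 0.5 SD per SD.

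| mood-to-marker effect | spurious share mediated | false positives | false positives with week-2 MADRS |
|---|---|---|---|
| 0 | 0% | 4.5% | 5% |
| 0.1 | 6% | 8% | 6% |
| 0.2 | 12% | 11% | 5% |
| 0.3 | 17% | 20% | 6% |
| 0.5 | 24% | 37% | 8% |

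If treatment does not itself move the marker, the unadjusted rate is at most 3%.

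**6. What adjustment can cost.** Suppose mediation is real and already acting by week 2, with a true mediator effect of 0.3, a 1 SD marker shift and no reverse path. The estimated indirect effect falls from −0.26 to −0.17 with week-2 MADRS and to −0.13 with weeks 2 and 4. Power falls from 76% to 62% to 47%.

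**The case against.** **SAP detail.** The covariates of a mechanistic model are often left to the SAP, which is not at hand, and the Protocol excludes none. That is fair. However, the Protocol does fix mediator, outcome, timing and test, and the moderation model just before it is stated as baseline-adjusted. As written, the mediation model does not deliver the stated aim.

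**Evidence for the mood-to-marker path.** A reader might infer from the Background that the Protocol accepts that mood lowers the markers under study. It does not. That sentence concerns IL-6 and TNF, and the markers analysed are HDL, LDL and CRP. Extending it to them is an assumption, which is why the range must include zero.

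**Baseline.** It would be wrong to say that baseline is ignored. The tested effect is stated in change scores, so baseline enters through them, though not as a separate covariate.

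**Adjustment.** A reader might infer that the week-2-adjusted fit should become the main model. Week-2 and week-4 MADRS are measured after randomisation and can be affected by treatment. Step 6 shows that adjusting for them can remove half of a true effect. The objection stands against replacement but not against a companion fit.

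**Consequence.** The Discussion is cautiously worded and the primary efficacy analysis is untouched. Both points stand. The Protocol's own caution that indirect effects must be relatively large concerns power and does not answer confounding.

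**Conclusion.** The point holds conditionally. The model as written cannot separate mediation from early mood acting on, or sharing causes with, the marker, and it cannot show a change that precedes clinical effect. With N = 120 and no true mediator effect, false mediation ranges from about 5% (mood-marker correlation 0) to 57-77% (correlation 0.4) for a 1 SD treatment effect on the marker. For a 0.3 SD effect it ranges from about 2% to 29%. These figures rest on assumed MADRS correlations and an assumed mood-marker correlation. The documents give neither.

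A reader might infer that a false mediation claim is to be expected. The documents do not support that: at zero correlation there is no bias, at 0.1 it is small, and nothing in the Protocol says which value applies to LDL, HDL or CRP.

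**What to change.** In the mediation paragraph of Statistical Analysis:

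- Include baseline MADRS and baseline biomarker as covariates in both the mediator and the outcome equation.
- Pre-specify a companion sensitivity fit that adds week-2 MADRS, which is measured before the mediator. The calculations above add it to the outcome equation; state whether it also enters the mediator equation.
- Add a further fit with week-4 MADRS, and report the reverse path from week-2 MADRS change to week-4 biomarker change.
- State that if the indirect effect does not persist after week-2 adjustment, it will be reported as an association and not as mediation preceding clinical effect.
- Reconcile Measurement of biomarkers (blood at baseline and week 12) with Table 1 (also week 4). Without a week-4 sample neither the planned model nor the companion fits can be run.

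The additions are wording and a few extra fits, since the MADRS ratings are already scheduled. The cost is interpretive: the adjusted fits remove any true mediated effect already expressed by week 2 or 4, so they are conservative and have lower power. They should stand beside the planned model and not replace it.

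### Mediation is tested by the proportion of the total effect mediated, which costs little power at the planned effect of 0.60 but a third to a half at 0.40 and most of it at about 0.30

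*Protocol*

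**What the plan says.** Protocol, Statistical Analysis (final paragraph, on mediation): "The mediation effect is tested by the proportion of the total effect from treatment group to change in MADRS" that runs through change in lipids or CRP. The next sentence names the software and has "the indirect effect estimated through bootstrap resampling". The paragraph closes with a caution about the sample size: "note the effect sizes for the indirect mediation pathway would need to be relatively large". It sets no condition on the total effect for using the proportion, and it does not name an interval or test of the indirect effect as the basis for concluding mediation.

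Earlier in the same section, the general rules are "Two tailed tests", "an alpha level of 0.05 will be used for significance", and a 95% confidence interval for every estimate.

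Protocol, Sample Size: "We estimate a moderate effect size of 0.60 will be reported at week 12", and "we will need to follow up 120 patients across the two groups to achieve 90" per cent power. The same paragraph cites "An effect size of 0.4 or greater for difference in MADRS scores in" placebo-controlled trials as the suggested mark of clinical utility for an antidepressant given as monotherapy.

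**The concern.** The proportion mediated is the indirect effect divided by the total effect. When the total effect is estimated imprecisely, its resampled values approach or cross zero. The ratio can then change sign or exceed 1, and its interval becomes very wide, even if the biomarker pathway is estimated reasonably well. The test then depends heavily on whether the primary comparison is itself clearly non-zero.

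What is at stake is the mechanistic hypothesis at the end of the Background, that lipid-lowering and anti-inflammatory effects mediate the response. If the clinical effect falls short of the planned value, a real pathway could be declared absent because the denominator was imprecise. The trial could also report a negative proportion, or one above 100%, that nobody can interpret.

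**Working it through.** **1. The plan's own figure.** For d = 0.60, two-sided 5% and 90% power, n per arm = 2(1.960 + 1.282)² / 0.60² = 58.4, so 59 (59.4 by the t-test, so 60). Sixty per arm gives 120 followed up, and 120 / (1 - 0.20) = 150 randomised. Power at 60 per arm is 90.8% (90.3% by the t-test). The sample size reproduces. The Protocol gives no power figure for mediation.

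**2. The denominator.** Unadjusted SE of the total effect, in SD units: √(1/60 + 1/60) = √(2/60) = 0.183.

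- 0.60 / 0.183 = 3.3 SE from zero, power 91%
- 0.40 / 0.183 = 2.2 SE, power 59%
- 0.30 / 0.183 = 1.6 SE, power 38%

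**3. Why the ratio inherits this.** In any resample the ratio is positive only when the indirect and total effects have the same sign. A 95% percentile interval for the ratio lies wholly above zero only if about 97.5% of resamples meet that condition. Once the indirect effect is clear, this is nearly the same as asking the total effect's interval to exclude zero.

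**4. Simulation.** Single-mediator model, 60 per arm: M = aT + error, Y = c′T + bM + error. The total effect is d = c′ + ab and the proportion mediated is ab/d. Within-arm SDs are 1, with no baseline adjustment. There were 500-800 trials per case and 600 bootstrap resamples stratified by arm. Two rules were compared: the 95% percentile interval of ab excludes zero, or that of ab/d does.

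These inputs are assumptions, not Protocol figures: a = 0.5, 1.0 or 1.5 SD, and true proportion 30%, 50% or 80%. In the central case a = 1.0 and 50% is mediated, so b = 0.5d: 0.30 at d = 0.60, 0.20 at 0.40 and 0.15 at 0.30.

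| Total effect | Indirect vs proportion, central case | Repeat run | Relative loss, central case | Relative loss, all cases |
|---|---|---|---|---|
| 0.60 | 93% vs 82% | 92% vs 82% | 11% | about 0-15% |
| 0.50 | 80% vs 60% | not run | 25% | 8-31% |
| 0.40 | 61% vs 34% | 58% vs 31% | 44% | 32-52% |
| 0.30 | 40% vs 12% | 39% vs 13% | 71% | 58-72% |

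Relative loss is (power for the indirect effect - power for the proportion) / power for the indirect effect. At 0.40 it is (61.2 - 34.2) / 61.2 = 44%.

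| Total effect | Estimates outside 0-1, all cases | Median 95% interval width for the proportion, all cases |
|---|---|---|
| 0.60 | 1-30% | 0.5-1.6 |
| 0.40 | 8-35% | 1.3-3.7 |
| 0.30 | 15-41% | 2.8-8.7 |

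The out-of-range percentages depend partly on how close the true proportion is to 0 or 1. The interval widths are the better guide: at 0.40 the typical interval is already wider than the whole 0-1 range.

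**5. False positives.** With b = 0 and a = 1.0 (800 trials), the proportion rejects in 5.5% of trials at d = 0.60 and 0.3% at d near zero. The indirect effect rejects in 6.5% and 7.0%. Simulation error at 5% is √(0.05 × 0.95 / 800) = 0.8 points, so the percentile interval for the indirect effect may be slightly liberal. An excess of 1.5 to 2 points does not explain a gap of 27 points at 0.40.

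**The case against.** The strongest reply is that the paragraph already contains the right quantity. The indirect effect is to be bootstrapped, all estimates are to carry 95% intervals, and the closing caution is about the indirect pathway. On that reading only one loosely worded sentence is at fault. This stands as far as it makes the repair easy. It does not change which quantity the Protocol says decides the test, and that is a stated choice rather than detail left to an analysis plan. The caution concerns the size of the indirect effect, whereas the extra loss comes from the denominator.

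A second reply is that mediation of a response presupposes a response, so a test that demands one is reasonable. The total effect already has its own primary test, however, and repeating that demand inside the mediation test costs power without adding information about the pathway.

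Third, baseline adjustment would sharpen the denominator. With an assumed baseline correlation of 0.3 to 0.6, the SE falls to about 0.17-0.15, which puts 0.40 at about 2.3-2.7 SE and 0.30 at about 1.7-2.1. That moves the loss towards smaller effects but does not remove it.

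A reader might infer that the proportion loses most of its power even at a moderate effect. The Protocol calls 0.60 moderate, and there the loss is at most about 15%. A reader might also get a starker contrast by holding the indirect effect fixed while the total shrinks. That sends the true proportion to exactly 1, where about half of all estimates exceed 1 at any sample size, and then beyond it, which needs a direct effect of opposite sign. Nothing in the Protocol suggests such a pattern, and the figures above do not rely on it.

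**Conclusion.** The point holds in a limited form. The Protocol tests mediation with a ratio that in effect also requires a clearly non-zero total effect. Under the assumed paths the cost is modest at the planned 0.60, about a third to a half of the power at 0.40, and most of it at about 0.30. Very wide intervals and estimates outside 0-1 become common as the total effect falls below the planned value. The exact sizes rest on the assumed mediator effect, proportion mediated and unadjusted model, but the direction is the same in every case at 0.50 and below.

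Two further inferences are not supported. Testing the indirect effect does not make this analysis well powered at small effects: in the central case its own power is only about 60% at 0.40 and 40% at 0.30. Nor does the point touch the primary MADRS comparison at week 12, which is a separate contrast. With no mediation and almost no total effect, the stated test errs towards missing mediation, not towards false claims of it.

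**What to change.** Reword the mediation paragraph so that the conclusion rests on the bootstrap 95% confidence interval of the indirect effect, which the paragraph already plans to estimate. State that the proportion mediated is descriptive, is given with its own interval, and is reported only when the 95% interval of the total effect excludes zero. Keep the existing caution about the size of effect needed.

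The cost is a wording change made before unblinding. The model, software, data collection and sample size stay as they are.
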